**Abstract**

**Background:** Men who have sex with men (MSM) bear a high burden of syphilis infection. Expanding syphilis testing to improve timely diagnosis and treatment is critical to improve syphilis control. However, syphilis testing rates remain low among MSM, particularly in low- and middle-income countries. We describe the protocol for a randomised controlled trial (RCT) to assess whether provision of syphilis self-testing services can increase the uptake of syphilis testing among MSM in China.

**Methods:** 444 high-risk MSM will be recruited online and randomized in a 1:1:1 ratio to (1) standard syphilis self-testing arm; (2) a self-testing arm program enhanced with crowdsourcing and a lottery-based incentive, and (3) a standard of care (control). Self-testing services include a free syphilis self-test kit through the mail at monthly intervals. Participants in the lottery incentive arm will additionally receive health promotion materials generated from an open crowdsourcing contest and be given a lottery draw with a 10% chance to win 100 RMB (approximately 15 US Dollars) upon confirmed completion of syphilis testing. Syphilis self-test kits have step-by-step instructions and an instructional video. This is a non-blinded, open-label, parallel RCT. Participants in each arm will be followed-up at three and six months through WeChat (a social media app like Facebook messenger). Confirmation of syphilis self-test use will be determined by requiring participants to submit a photo of the used test kit to study staff via secure data messaging. Both self-testing and facility-based testing will be ascertained by sending a secure photographic image of the completed kit through an existing digital platform. The primary outcome is the proportion of participants who tested for syphilis in the past three months.

**Discussion:** Findings from this study will provide much needed insight on the impact of syphilis self-testing on promoting routine syphilis screening among MSM. The findings will also contribute to our understanding of the safety, effectiveness and acceptability of syphilis self-testing. These findings will have important implications for self-testing policy, both in China and internationally.

**Trial registration:** ChiCTR1900022409 (10 April, 2019)

**Background**

Men who have sex with men (MSM) are disproportionately affected by syphilis worldwide. The WHO estimates the prevalence of syphilis among MSM is 5% or more in at least 42 countries (15 countries in Asia including China with a prevalence of 5.1%), 10% or more in 20 countries ( 6 countries in Central America and 5 countries in South America ) and more than 20% in eight countries including 3 Pacific Island countries and 2 South American countries [[1](#_ENREF_1)]. Expanding access to syphilis testing so that individuals receive a timely diagnosis and treatment, plays a key role in the control of syphilis transmission [[2](#_ENREF_2)]. Evidence shows that for men who are HIV positive and/or MSM, screening every three months (compared with screening every six or twelve months) is associated with increased detection rates at various stages of syphilis infection [[3-7](#_ENREF_3)]. Increases in syphilis screening frequency are associated with increased detection of early asymptomatic syphilis with relative falls in secondary syphilis for both HIV-positive and HIV-negative MSM in Australia, suggesting a possible interruption of syphilis progression [[8](#_ENREF_8)].

However, given the cost of the tests, anticipated stigma, and the infrastructure requirements, syphilis testing rates are generally low, especially in resource-limited settings. Previous research shows that only 30% of Chinese MSM have ever tested for syphilis [[9](#_ENREF_9)]. Whilst traditional testing for syphilis is health facility-based, recent advances in testing techniques, including dried blood spots, point-of-care testing, and self-testing, have enabled decentralized testing strategies [[10](#_ENREF_10)]. Among these innovations, self-testing offers a great potential to expand syphilis testing among hard-to-reach populations due to its convenience, confidentiality, and relatively high sensitivity and specificity [[11](#_ENREF_11), [12](#_ENREF_12)]. Evidence from HIV self-testing studies have demonstrated its effectiveness in increasing HIV testing frequency among MSM in a variety of settings [[13-15](#_ENREF_13)]. In view of this, WHO subsequently released guidelines recommending HIV self-testing [[16](#_ENREF_16)].

Though not yet approved by the China Food and Drug Administration, syphilis self-test kits are currently available for purchase in China, mainly through online retailers [[17](#_ENREF_17)]. In 2018, we conducted a nationwide Internet survey to explore the prevalence of and correlates of syphilis self-testing uptake among MSM in China. Results showed that half of MSM who ever tested for syphilis had ever used a self-test. Self-testing potentially reached MSM who would not otherwise have attended health facilities for testing [[18](#_ENREF_18)]. Several studies in literature have explored the use of syphilis self-testing among MSM [[12](#_ENREF_12), [19-21](#_ENREF_19)], few studies have examined the effectiveness of intervention strategies which found that Internet-based strategy, such as using Facebook or smartphone applications, could be an effective way to promote syphilis self-testing uptake. Further evidence to inform the design of interventions by using self-testing to promote routine syphilis screening and linkages to care and treatment among MSM is needed.

Economic incentives (cash or in-kind rewards) to promote healthy behaviors are becoming increasingly common and have been suggested as an effective approach to promote healthy behaviors [[22](#_ENREF_22)]. We found Chinese MSM who had higher risk attitudes and who reported riskier sexual behaviours indicated greater interest in taking a syphilis testing for the opportunity to participate in a lottery draw [[23](#_ENREF_23)]. Thus, lottery incentive may be useful in promoting syphilis screening among high risk MSM. However, the mode of the lottery and the amount of incentives are unknown. Crowdsourcing organizes a group of non-experts and experts to solve a problem, which presents a promising strategy in creating effective intervention for the target populations [[24](#_ENREF_24)]. This approach has demonstrated effectiveness in increasing HIV testing by 43% among MSM and spurred community engagement [[25](#_ENREF_25)]. Thus, to enhance the syphilis self-testing with lottery incentive by using crowdsourcing may be a promising way for service delivery.

The purpose of this protocol manuscript is to describe a randomized controlled trial that will determine the effectiveness of two syphilis self-testing strategies compared to conventional facility-based syphilis testing.

**Methods/design**

**Study objectives**

This randomized controlled trial (RCT) is designed to determine whether provision of syphilis self-testing increases the proportion of participants who tested for syphilis during the trial among MSM in China. In addition, this study also aims to explore whether integration of a crowdsourced lottery incentive can further enhance the promotion of syphilis testing and linkage to care, after testing positive, among MSM in China.

**Study design**

This is a non-blinded, open-label, parallel RCT with individuals randomized in a 1:1:1 ratio to three study arms: control arm (standard of care); standard syphilis self-testing arm; and lottery incentivized syphilis self-testing arm. Control arm participants will receive information on self-referral pathways for free facility-based syphilis testing. Both self-testing arms will be offered to access syphilis self-test kits for free at monthly intervals. Participants in each arm will be followed-up for six months (Figure 1). The study hypothesis had been tested in a pilot study, completed in October 2019, which examined the feasibility of implementing the self-testing and crowdsourced lottery incentivized syphilis self-testing model among 145 Chinese MSM. The pilot study showed that both standard self-testing arm (0.74) and lottery incentivized arm (0.70) increased the frequency of syphilis testing more than the control arm (0.36). Preliminary data from this pilot study was used to inform this definitive trial design. Preliminary results are available on the supplement materials. The definitive trial, outlined in the current trial protocol, has begun in December 2019, and is expected to be completed in July 2020.

**Study setting and population**

Participants will be recruited from a large MSM-oriented mobile social app - Blued (Danlan, Beijing, China). Blued is China's most popular social networking mobile application among MSM. By February 2018, Blued had 40 million registered users globally, with 70% in Mainland China [[26](#_ENREF_26)].

Participants are eligible if they: are born biologically male; aged 18 years or above; had unprotected anal sex with other men in the past twelve months; reported not testing for syphilis in the last six months; not currently living with syphilis; plan to live in China for the next six months; and have a stable residence where they can securely receive a postal package. Participants are excluded if they: are participating in another research programme that is related to HIV/STIs or cannot provide consent.

**Arms and Interventions**

Arms and interventions are summarized in Table 1.

**1. Control arm:** Participants in the control arm will be provided information about local STD services and encouraged to uptake free syphilis testing at their local STD or HIV voluntary testing and counseling (HTC) clinics. HTC clinics in China provide both HIV and syphilis testing free of charge. Participants will be encouraged to screen for syphilis every three months. Reminder will be sent by SMS or WeChat (a social media app like Twitter and Facebook, commonly used in China) three monthly (enrollment, three-month, and six-month) during six months study period.

**2. Standard self-testing arm**: In addition to being prompted to uptake syphilis testing at local facilities, participants in this arm will be provided with access to syphilis self-testing along with the reminders. Participants may request order of syphilis self-testing packages through WeChat with the package being sent to participants by postal mail (express delivery). The provision of syphilis self-testing service will last for six months. Participants order self-testing package online with maximum oneself-testing package per month.

**3. Lottery incentivized self-testing arm**: In this arm, the participant will be provided with both control arm and standard syphilis self-testing arm interventions. In addition, participants who confirm that they have tested for syphilis during the trial period either through self-testing or facility-testing will be given a lottery draw. The lottery draw will provide a 10% chance of winning 100 RMB (equal to 15 US Dollars). The procedure, value and probability of the lottery scheme was determined by a previous open crowdsourcing contest. We solicited 14 lottery schemes via an open crowdsourcing contest. The winning entries were then used to develop the aforementioned lottery incentivizes to be used in the current study.

**Table 1 Arms and interventions information**

| **Arms** | **Intervention description** | **Intervention delivery** |
| --- | --- | --- |
| **Control arm** | 1. **Test prompts**: information about risk of syphilis infection and local free syphilis test services. | - Text messages will be sent at enrollment, three-month visit, and six-month visit via WeChat. - Voluntary report testing result to the platform. |
| **Standard self-testing arm** | 1. **Test prompts**: information about risk of syphilis infection and local free syphilis test services.  2. **Self-testing**: free home delivery of self-testing package. | - Text messages will be sent at enrollment, three-month visit, and six-month visit via WeChat. - Provision of syphilis self-testing service: self-testing package can be ordered online and sent to participant through postal mail. Maximum oneself-testing package per month. - Voluntary report self-test result to the platform. |
| **Lottery incentivized self-testing arm** | 1. **Test prompts**: information about risk of syphilis infection and local free syphilis test services.  2. **Self-testing**: free home delivery of self-testing package.  3. **Lottery incentive**: lottery draw with 10% chance to win 100 RMB for participants have confirmed uptake of syphilis testing. | - Text messages will be sent at enrollment, three-month visit, and six-month visit via WeChat. - Provision of syphilis self-testing service: self-testing package can be ordered online and sent to participant through postal mail. Maximum one self-testing package per month. - Voluntary report self-test result to the platform. - Lottery draw will be given to participants who get syphilis tested and upload photo verification to the platform. |

***Syphilis self-testing kit***

The HIV self-testing practice in China, using rapid test kits for self-testing, has shown good acceptability, feasibility, and safety [[11](#_ENREF_11), [12](#_ENREF_12), [27](#_ENREF_27)]. In this trial, we will use the syphilis and HIV combo rapid test kit (SD BIOLINE Syphilis/HIV Duo). The SD BIOLINE Syphilis/HIV Duo test is a solid phase immunochromatographic assay for the qualitative detection of antibodies to all isotypes (IgG, IgM, and IgA) specific to HIV-1/2 and/or Treponema pallidum (TP) simultaneously in human serum, plasma, or whole blood. The sensitivity and specificity for syphilis is 99.67% and 99.72% respectively [[28](#_ENREF_28)]. Our pilot trial results showed that the overall satisfaction with the use of syphilis self-testing was 100%. The syphilis self-testing package will be equipped with the manufacturer-supplied step-by-step instructions and a web-link (Source link: https://www.alere.com/en/home/support/product-demos/sd-bioline-hiv-syphilis-duo.html) to an instructional video.

**Outcomes Measures**

The primary outcome is the proportion of participants who tested for syphilis during the trial. Syphilis tests may be either at a clinic or via self-test. This will be verified in all participants using photo-verification. We will additionally look at the incremental benefit of the lottery incentive efficacy in promoting syphilis, number of newly identified syphilis infections, the linkage to syphilis clinical care after self-testing, the proportion of HIV and other STIs (chlamydia, gonorrhea) tests among the participants who use self-testing and cost-effectiveness of syphilis self-testing in promoting uptake of syphilis testing among Chinese MSM.

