**Surveys**

**Baseline:** All participants complete a self-administered survey on an online survey platform (Wen Juan Xing, https://www.wjx.cn) at enrolment. The baseline survey includes questions on socio-demographic characteristics, sexual behaviors, past HIV/syphilis testing and treatment, and attitude towards syphilis self-testing.

**Follow-up surveys:** Participants in the three arms of the study will complete a brief online survey at three-monthly intervals. The follow up surveys collects information on the number, time, location, reasons for, and results of syphilis tests (including self-tests) and other STI tests at clinics and community sites, and sexual risk behaviors in the past three months. Participants in the two self-testing arms are also asked about the number of self-test kits they used to test their sexual partner(s) or if they gave any kits to someone else to test. At the last follow-up, participants will be asked to get STD (HIV, syphilis, chlamydia, and gonorrhea) screening test in their nearby clinic. The testing fee will be redeemed by an upload of the test results. Participants will be provided with 30 RMB (equal to 4 US Dollars) for their time to complete each follow-up survey.

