**Statistical methods**

***Sample size***

According to our initial pilot study (***Supplementary material***), the proportion of individuals who undertook a syphilis test was 0.36 (95% confidence interval: 0.22 – 0.52) at the one-month follow-up in the control arm. This increased to 0.74 (95% confidence interval: 0.61 – 0.81) in the self-testing arm. On this basis, for the primary outcome with 80% statistical power and type I error probability of 0.05, we conservatively estimate a sample size of 29 per arm (including 20% loss to follow up [25]) for this study. According to our previous experience on using the crowdsourced HIV self-testing intervention in increasing HIV testing among MSM (the proportion was 0.85 [25]), we estimate a sample size of 148 for each arm to achieve 80% power to detect a difference between the crowdsourced lottery incentivized self-testing arm and standard syphilis self-testing arm. Finally, a total of 444 (148 per arm) will be enrolled in this trial.

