#### *Analysis plan*

Data will be retrieved from the online survey platform. De-identified datasets and codebook will be stored for statistical analysis. The syphilis testing proportion in each arm (control, standard self-testing, and lottery incentivized self-testing) will be assessed using an intention-to-treat analysis during the follow-up period, excluding confirmatory tests after a reactive self-test.

The effects of the intervention will be measured by comparing the differences in proportions of men who take syphilis testing during two rounds of follow up by using generalized estimating equation (GEE) model. We will use the chi-square test to compare differences in the proportion of linkage to syphilis clinical care, have HIV and other STI (chlamydia, gonorrhea) testing performed, and have condomless sex events with different partners within six months of randomization across three groups and use post-host test to check the significance of differences between each of the two groups.

We will estimate the total and incremental unit costs for each arm. All costs will be identified as start-up costs, fixed costs and variable costs. Start-up costs are incurred during the process of creating this study (e.g. survey platform coordination). Fixed costs are costs that do not change with an increase or decrease in the number of people served during the trial period (e.g. administration, office equipment). Variable costs are expenses that vary with the number of participants served (e.g. recruitment, supplies, postage fee). We will first calculate the total cost for each group, then divided these costs by the number of men tested and the number of newly identified syphilis cases detected in each study arm to obtain the incremental unit costs. In addition, we will build a decision tree model using a healthcare provider perspective to estimate the incremental cost for per additional person tested and case identified for each intervention will be calculated. Univariate, multivariate and probabilistic sensitivity analyses will be conducted to test the robustness of our results.

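### The protocol states two different primary outcomes (tested in the past three months, or ever tested in the six-month trial), and the two-round GEE fits only the per-round one naturally

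*Protocol*

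**What the plan says.** - Protocol, Outcomes Measures: "The primary outcome is the proportion of participants who tested for syphilis during the trial". The Study objectives use the same window: the trial asks whether self-testing "increases the proportion of participants who tested for syphilis during the trial among MSM in China". Under Study design, "Participants in each arm will be followed-up for six months".
- Protocol, Abstract: "The primary outcome is the proportion of participants who tested for syphilis in the past three months". It does not say at which visit.
- Protocol, Analysis plan: the testing proportion in each arm "will be assessed using an intention-to-treat analysis during the follow-up period, excluding confirmatory tests after a reactive self-test". The next paragraph measures the effect by comparing proportions of "men who take syphilis testing during two rounds of follow up by using generalized estimating equation (GEE) model".
- Protocol, Surveys: surveys are three-monthly, and the stated recall window closes the list of items ("sexual risk behaviors in the past three months"). At the last follow-up, participants in all arms are asked to have a clinic STD screen that includes syphilis.
- Protocol, Sample size: the control proportion of 0.36 was observed in the pilot "at the one-month follow-up in the control arm". The 0.74 for self-testing follows directly. The 0.85 comes from an earlier HIV self-testing study, with no window given.

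**The concern.** Ever tested in six months gives one yes/no value per man. Tested in the past three months, taken at months 3 and 6, gives two correlated values per man. The proportions, the differences between arms and the precision are not the same. A man who tests once in six months is a full success under the first definition and a success in one round of two under the second.

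The Analysis plan does not settle the matter. Its first paragraph describes a proportion over the whole of follow-up, and its second describes a model over two rounds. A reader cannot tell which number will be the primary result.

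The window also governs how the clinic screen at the last follow-up is treated. The Analysis plan excludes only confirmatory tests after a reactive self-test. A test that the study itself asks of every arm could therefore enter the primary outcome and pull the arms together.

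**Working it through.** **The plan's own sample sizes.** Two proportions, unpooled variance, two-sided alpha 0.05, power 80%: n = (1.96 + 0.84)² × [p1(1−p1) + p2(1−p2)] / (p1−p2)², then divided by 0.8 for 20% loss.

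- 0.36 vs 0.74: 7.85 × 0.4228 / 0.1444 = 23; 23 / 0.8 gives 29. This matches the stated 29 per arm.
- 0.70 vs 0.85: 7.85 × 0.3375 / 0.0225 = 118; 118 / 0.8 gives 148. This matches the stated 148.
- 0.74 vs 0.85: 7.85 × 0.3199 / 0.0121 = 208; 208 / 0.8 gives 260.

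The 148 thus reproduces from 0.70 (the pilot lottery-arm value in Study design), not from the 0.74 that Sample size gives for standard self-testing. That is a separate matter, but for this reason both pairs are shown below.

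**Assumptions for comparing the two definitions.** The documents give no three-month or six-month proportions. I take the planning values as per-round (three-month) values, use 118 evaluable per arm (148 × 0.8), and let the within-person correlation r between rounds run from 0 to 1, equal in the arms compared.

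- Ever-tested proportion: P = 1 − [(1−p)² + r·p(1−p)].
- Ever-tested SE: √{[P1(1−P1) + P2(1−P2)] / 118}.
- Two-round average SE: √{[p1(1−p1) + p2(1−p2)] / 118 × (1+r)/2}.
- Power = Φ(difference/SE − 1.96).

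**Control vs standard self-testing, r = 0.** Ever-tested is 1 − 0.64² = 0.590 against 1 − 0.26² = 0.932, a difference of 34 points. Per round it is 0.74 − 0.36 = 38 points. Power is near 100% under both.

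**Lottery vs standard, 0.74 vs 0.85, r = 0.**

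- Ever-tested: 0.932 vs 0.978, difference 0.045, SE 0.0268, power Φ(1.68 − 1.96) = 39%.
- Two-round average: difference 0.11, SE 0.0368, power Φ(2.99 − 1.96) = 85%.

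| Per-round pair | r | Ever-tested | Power, ever-tested | Power, two-round average |
| --- | --- | --- | --- | --- |
| 0.74 vs 0.85 | 0 | 0.932 vs 0.978 | 39% | 85% |
| 0.74 vs 0.85 | 0.5 | 0.836 vs 0.914 | 44% | 68% |
| 0.74 vs 0.85 | 1 | 0.740 vs 0.850 | 56% | 56% |
| 0.70 vs 0.85 | 0 | 0.910 vs 0.978 | 62% | 98% |
| 0.70 vs 0.85 | 0.5 | 0.805 vs 0.914 | 68% | 90% |
| 0.70 vs 0.85 | 1 | 0.700 vs 0.850 | 80% | 80% |

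At r = 1 the two definitions coincide. If dependence differs by arm, the ever-tested lottery difference is not confined to 4.5 to 11 points. With 0.74 vs 0.85 it runs from 0.850 − 0.932 = −8 points (standard independent, lottery fully dependent) to 0.978 − 0.740 = +24 points (the reverse).

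**The case against.** The objective and the Outcomes Measures section agree, so the Abstract could be treated as a slip and the six-month reading as the intended one. That is a fair reading. It still leaves the two-round GEE without a repeated outcome. A GEE can technically be fitted to one value per man, and the same section also speaks of the whole follow-up period, so the GEE alone does not prove that a per-round outcome was meant. The Analysis plan is mixed rather than decisive.

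Three stronger readings are tempting, and the documents do not support them.

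- A reader might infer that the main question is at risk. It is not: control vs standard self-testing keeps power near 100% under both definitions. The loss falls on lottery vs standard, which the objectives call exploratory, although it does set the enrolment of 444.
- A reader might infer that the outcome will be chosen once results are known. Two stated definitions leave room for that, but a SAP that is not shown may fix one. The Blinding section also says outcome assessors are blinded, although the Abstract and Study design call the trial non-blinded.
- A reader might infer that the whole sample size rests on one-month proportions. One month is written for the control value and implied for 0.74, which together give the 29. The 148 also depends on 0.85, which has no stated window.

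**Conclusion.** The protocol contradicts itself on its primary outcome, and nothing in it resolves the conflict. Each statement is a complete sentence, so this is not an extraction fault, and a SAP that settles the definition would still leave the protocol inconsistent.

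The practical size depends on the comparison. It is small for control vs standard self-testing. For lottery vs standard with independent rounds it is large: about 39% power for ever-tested against 85% for the two-round average (0.74 vs 0.85), or 62% against 98% (0.70 vs 0.85). The gap shrinks to nothing as within-person dependence becomes complete. These figures are illustrations: they carry the planning proportions over to three-month rounds and assume equal dependence in both arms. The contradiction itself needs no assumption.

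**What to change.** Before outcome data are examined by arm, state one definition in the Abstract, Study objectives, Outcomes Measures and Analysis plan.

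- The definition that fits the planned GEE: at least one verified syphilis test in the preceding three months, assessed at months 3 and 6. The primary estimate is the risk difference averaged over both rounds. Ever tested within six months becomes secondary.
- If the sponsor prefers to keep the definition in the objectives and Outcomes Measures: correct the Abstract, and replace the two-round GEE with a single risk difference on ever-tested.

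Under either choice, state that the clinic syphilis test requested of all arms at the last follow-up does not count toward the primary outcome. In Sample size, say that 0.36 and 0.74 are pilot proportions (one-month, as written for the control arm), that 0.85 comes from an earlier HIV self-testing study with no stated window, and that all three are carried over as assumptions for the chosen window.

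No new data are needed: verified tests are collected, and the three-monthly surveys record the number and time of tests, so both versions can be derived. Because the protocol says the trial began in December 2019, the change should be a dated amendment stating that outcomes by arm had not been seen.

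### HIV/STI testing and linkage to care are defined among men who self-test but tested across the three randomised arms, and HIV testing says nothing among users of the trial's dual kit

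*Protocol*

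**What the plan says.** Outcomes Measures in the Protocol names two secondary outcomes that depend on self-testing: "the linkage to syphilis clinical care after self-testing", and "the proportion of HIV and other STIs (chlamydia, gonorrhea) tests among the participants who use self-testing".

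The Analysis plan assigns the test: "We will use the chi-square test to compare differences in the proportion of linkage to syphilis clinical care". The same sentence covers the proportion who "have HIV and other STI (chlamydia, gonorrhea) testing performed", and places the comparison "within six months of randomization across three groups", followed by pairwise post-hoc tests. It does not restrict the comparison to men who self-test.

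Three other statements matter:

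- **Control arm.** Study design says "Control arm participants will receive information on self-referral pathways for free facility-based syphilis testing". Table 1 lists kit delivery only for the two self-testing arms.
- **Kit.** The kit section says "we will use the syphilis and HIV combo rapid test kit", so one use tests for both infections.
- **Final screen.** The Surveys section asks participants, without limiting it to an arm, to have HIV, syphilis, chlamydia and gonorrhoea tests at a clinic at the last follow-up, with the fee refunded.

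**The concern.** The outcome definition and the test do not describe the same men. Under Outcomes Measures the denominator is a group formed after randomisation by a behaviour that two arms are supplied to perform and control is not. Even the lottery-versus-standard contrast conditions on a behaviour that the incentive is meant to change. Under the Analysis plan the denominator appears to be everyone randomised.

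The choice changes what the result means. A difference in HIV testing could be read as a wider benefit of self-testing when it mainly shows which kit was posted. Linkage is one of the aims that the Study objectives give the lottery arm, yet it can be observed only in men with a positive result, who may be few. A chi-square test with pairwise follow-up on such a subset could be reported as randomised evidence, which it is not.

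**Working it through.** The Protocol gives no figure of its own for these outcomes. The check compares the two readings and then sizes the groups.

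**Inputs**
- 148 men per arm (Sample size).
- Proportion tested by any route: 0.36 control, 0.74 standard and 0.70 lottery in the pilot (Study design). The Sample size section uses 0.85 for the lottery arm, taken from an earlier crowdsourced HIV self-testing study.
- 5.1% syphilis prevalence among MSM in China (Background), used here as an assumed reactive proportion. 10% is a second assumption, to show a range.
- Share of control testers who bought a kit: not given. 10%, 25% and 50% are assumed. The Background reports that half of MSM ever tested had at some time used a self-test.

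**Reading 1: denominator is self-testers (Outcomes Measures)**

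Expected testers by any route = 148 × proportion tested:
- control 148 × 0.36 = 53.3
- standard 148 × 0.74 = 109.5
- lottery 148 × 0.70 = 103.6 (148 × 0.85 = 125.8)

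Control self-testers = 53.3 × assumed share = 5.3, 13.3 or 26.6. None has a trial-supplied kit. The self-testing arms would have about 110 and 104 to 126 if all testing there were self-testing.

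Every man who uses the trial kit on himself has also had an HIV test. At the pilot proportions the standard-versus-lottery table is 110 of 110 against 104 of 104. The not-tested column is zero, its expected counts are zero, and the chi-square statistic is undefined. Any variation would come from men using other kits, mainly in control.

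**Reading 2: denominator is all randomised men (Analysis plan)**

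The test can be computed and compares randomised arms. But each trial-kit user counts as HIV-tested. If all testers in the self-testing arms used the kit, kit use alone gives 110/148 = 0.74 and 104/148 = 0.70. These are the syphilis-testing proportions again. Chlamydia and gonorrhoea are not on the kit, so they are not inflated in this way. All of these tests can also be prompted by the study's own final screen.

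**Linkage: expected reactive men = 148 × proportion tested × proportion reactive**

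| Arm | 5.1% reactive | 10% reactive |
|---|---|---|
| Control (0.36) | 2.7 | 5.3 |
| Standard (0.74) | 5.6 | 11.0 |
| Lottery (0.70 to 0.85) | 5.3 to 6.4 | 10.4 to 12.6 |

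These counts use testing by any route. Limiting control to self-testers gives 53.3 × 0.10 × 0.051 = 0.3 up to 53.3 × 0.50 × 0.051 = 1.4 reactive men.

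Expected cells in each row are (row total) × p and (row total) × (1 − p), where p is the overall linkage proportion. A row total below 10 cannot have both cells at 5 or more. At 5.1% all three rows are below 10, and the control row is below 5 outright, so at least four of the six cells fall below 5 whatever p is. At 10% the control row (5.3) still has at least one such cell.

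**The case against.** The strongest defence is that the Analysis plan means what it says: three randomised groups, everyone counted. On that reading the HIV/STI comparison is computable and randomised, and the fault is one loose phrase in Outcomes Measures. This stands in part. It rescues the test, but it leaves the two sections in contradiction and does not remove the kit's mechanical effect on HIV testing.

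A reader might go further and infer that control has no self-testers at all. The documents do not support that. The Discussion accepts that control men may buy kits online and says that testing method will be recorded in each group. The control denominator is small and self-selected, not certainly empty.

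A reader might also infer that the whole HIV/STI outcome is fixed at 100%. That holds only for HIV and only for users of the trial kit. The Protocol does not say what kits bought elsewhere test for, and chlamydia and gonorrhoea are outside the kit.

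The sparse-cell argument is not certain either. The 5.1% is a national estimate. The trial enrols high-risk men, and the Discussion notes that treponemal tests cannot separate past from current infection, so more men could react. The exclusion of men currently living with syphilis pulls the other way. The control figure of 0.36 is a one-month pilot result, while this trial runs six months. If 90% tested and 10% reacted in every arm, each would have 148 × 0.9 × 0.1 = 13.3 reactive men. At 50% linkage every expected cell would then be 6.7. The choice of an exact test could also be left to a statistical analysis plan. The conflict over population should not be, because the Protocol states both versions.

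**Conclusion.** The point holds as a conflict over the population for secondary outcomes. Outcomes Measures and the Analysis plan cannot both be followed. Under the first, contrasts with control are not randomised comparisons and HIV testing carries no information among trial-kit users. Under the second, the comparison is valid in form, but HIV testing in the kit arms largely restates kit uptake.

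That conclusion rests on the Protocol's wording and on the dual kit, not on the assumed figures. The claim that reactive men are likely to be few does depend on them: about 2.7, 5.6 and 5.3 to 6.4 per arm at 5.1%, and about 5, 11 and 10 to 13 at 10%. It should be stated as likely, not as fact. The primary outcome is not affected.

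**What to change.** Use one population in both sections.

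1. **HIV and chlamydia/gonorrhoea testing.** Define each over all randomised men, within six months of randomisation, counting tests done before the study-requested screen at the last follow-up. Report chlamydia/gonorrhoea separately from HIV.
2. **HIV.** Report any HIV test and, separately, any HIV test other than the trial kit. The second shows whether testing changed beyond the posted kit.
3. **Linkage.** As the randomised comparison, report the number confirmed and linked over all randomised men in each arm. Alongside it, report linkage among men reactive by any route, labelled as a non-randomised description, with exact confidence intervals by arm or Fisher's exact test in place of the three-group chi-square.

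The cost is mainly wording. The follow-up surveys already ask for the number, time and place of syphilis and other STI tests, and the Discussion says testing method will be recorded in each group. The team should confirm that HIV tests are dated and that the trial kit can be told apart from other tests.

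There are two drawbacks. Linkage will be reported with less apparent precision. Linkage over all randomised men also combines testing uptake with linkage after a positive result, which is why the descriptive figure should stand beside it.
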